### Recruitment

The coordinating researcher of the APPtimize trial will screen weekly the colorectal outpatients clinic lists per centre for eligible participants. The treating physician will be asked to get permission from the patients to be approached by the coordinating researcher. The treating physician hands out the Patient Information Form (PIF) when patients agree to be approached by the coordinating researcher. After permission to be approached and ‘informed consent for screening’ is obtained, the coordinating researcher will call the patient to explain the study and address any questions the patient may have after reading the PIF. After the telephone conversation, patients will be granted a reasonable amount of decision time - at least a minimum of 72 h - to decide whether they want to participate. Reasons of refusing participation will be registered and patients are asked permission for collection of postoperative outcome parameters. After obtaining written consent, participants will be randomized.

### Group allocation and blinding

After inclusion, participants are randomly assigned to the mobile application (intervention) group or standard care (control) group in a 1:1 ratio, using an internet randomization module with stratification for benign or malignant pathology and age (> 50 years and < 50 years). Random block sizes of 2, 4, and 6 will be used. The coordinating researcher will initiate the allocation sequence and following study enrolment.

Participants, professionals of the healthcare team, and outcome assessors will not be blinded to the treatment allocation. Patients will be instructed to not tell other patients in their ward if they were assigned to the intervention or control group.

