## Background

The Enhanced Recovery After Surgery (ERAS) Society was formed in 2001 by a group of European surgeons to optimize clinical outcomes of patients undergoing surgery. Initially the ERAS Study Group published a consensus document with a scientific, evidence-based approach about the perioperative care for colonic resections (2005) and colorectal surgery (2009) [1]. Compared to routine care in elective colonic surgery, application of the ERAS protocol proved to reduce surgical stress, resulting in a better postoperative physiological status of the patient and improved mobilization short-term after surgery [2–6]. These outcomes contribute to faster postoperative recovery, shorter length of stay in hospital (LOS), and reduced rates of morbidity [7–9]. Nowadays, the ERAS protocol consists of 24 core elements (Table 1), and in order to successfully implement these 24 elements, a multidisciplinary team of anaesthetists, surgeons, nurses, physiotherapist and dieticians is essential. Local ERAS protocols, based on the ERAS guideline, can vary depending to the performing medical centre. The ERAS protocol elements are divided into preadmission, preoperative, intraoperative and postoperative phases, which, in their synergy, improve recovery after surgery [10]. An element is considered ‘active’ when some or full contribution of the patient is required. Elements are ‘passive’ when they do not directly depend on or require patient’s actions (Table 1) [11].

**Table 1 Tab1:** ERAS society guideline elements for colonic resections

Element	Responsible professional	Involvement patient
Preadmission		
1 Cessation of smoking and excessive intake of alcohol	Surgeon, patient	Active
2 Preoperative nutritional screening and, as needed, assessment and nutritional support	Surgeon	Active/Passive
3 Medical optimization of chronic disease	Anaesthetist	Passive
Preoperative		
1 Structured preoperative information and engagement of the patient and relatives or caretakers	Nurse	Passive
2 Preoperative carbohydrate treatment	Nurse	Active/Passive
3 Preoperative prophylaxis against thrombosis	Surgeon	Active/Passive
4 Preoperative prophylaxis against infection	Anaesthetist	Passive
5 Prophylaxis against nausea and vomiting	Anaesthetist	Passive
Intraoperative		
1 Minimal invasive surgical techniques	Surgery	Passive
2 Standardized anesthesia, avoiding long-acting opioids	Anaesthetist	Passive

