## Methods

### Study setting

The ERAS APPtimize study is a multicentre RCT that will be conducted in the Amsterdam University Medical Centres (UMCs), locations AMC and VUMC, in the Netherlands. APPtimize is a blended word, combining ‘APP’ and ‘timize’ from ‘application’ and ‘optimization’. The SPIRIT (Standard Protocol Items: Recommendations for Interventional Trials) 2013 statement will be followed and the trial will be reported in accordance to the CONSORT-EHEALTH(Consolidated Standards of Reporting Trials of Electronic and Mobile Health Applications and online TeleHealth) checklist V1.6.2. A completed informed consent form is required to participate in this study. The ERAS APPtimize study will be conducted in line with the declaration of Helsinki. Approval of the local medical ethics committee for this study was obtained (registration number NL63874.018.17) and the study is registered at the Netherlands Trial Registry (NTR7314).

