### Study population

The study population consists of patients scheduled to undergo colorectal surgery for either benign or malignant conditions. Patients must be 18 years or older and in possession of a smartphone operating iOS 9 (release date: September 16, 2015) and up or android 8.0 (release date: August 21, 2017) and up. Participants who meet one or more of the following criteria will not be considered for inclusion:

Exclusion criteria:
Palliative surgery or surgery following neo-adjuvant radio- or chemotherapyElective surgery for previously established complications (e.g. enteral fistula, presacral abscess) with the exception of colostomy correctionPatients with a Karnofsky score ≤ 40Incompetence of understanding the Dutch languageVisual impairment, unless well corrected with visual aidsPhysical or mental disabilities limiting the use of a mobile applicationWhen pre-operatively is estimated by the treating surgeon that adherence to the ERAS protocol postoperative is not feasibleIf expected LOS is 3 days or less after surgeryMultiple organ resection

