### Investigational intervention

#### Content development

A consensus meeting was organized with a multidisciplinary team of caregivers, representing both Amsterdam UMCs’ locations. Both locations practice almost all the elements from the 2012 ERAS society recommendations for colorectal surgery as part of their ‘care as usual’ except for ‘nutritional screening’ and ‘chewing gum as a laxative’. [9] Active ERAS elements, elements that depend on patient involvement, were included in the application. The multidisciplinary team of caregivers evaluated the ERAS elements for their eligibility to be included in the application. Although ‘nutritional screening’ was not part of current ‘care as usual’, the multidisciplinary team thought it would be useful to include this element in the application. Table 2 displays all elements that were included in the application. In ‘Additional file 1’, one can find the functional design of the application. The functional design illustrates the workflow through the application and the basic layout. After the first version of the application will be developed, ‘patient experts’ will be invited to test the application and review the content of the application.

**Table 2 Tab2:** ERAS elements in the APPtimize application

Preadmission	
1. Cessation of smoking and excessive intake of alcohol	
2. Preoperative nutritional screening and, as needed, assessment and nutritional support	
Preoperative	
3. Preoperative carbohydrate treatment	
4. Preoperative prophylaxis against thrombosis	
Postoperative	
5. Early mobilization (day of surgery)	
6. Early intake of oral fluids and solids (offered the day of surgery)	
7. Early removal of urinary catheters and intravenous fluids (morning after surgery)	
8. Use of laxatives	
9. Intake of protein and energy-rich nutritional supplements	
10. Prepare for early discharge	

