### Data analyses

Statistical analyses of any difference between the two study groups will be performed using SPSS for Windows version 25 or higher (SPSS Inc. Chicago, IL). Data will be analysed according to intention to treat protocol. If applicable, missing data will be imputed. Baseline characteristics will be summarized using descriptive statistics and compared between the intervention and control groups. Continuous data will be reported as mean and standard deviation in case of normal distribution and as median 95% confidence intervals in case of non-normal distribution. Normality of the data distribution will be analysed by visually inspecting the histograms and Kolmogorov-Smirnov test. Comparative analysis will be done using a two-sided t-test in case of normal distribution and by means of the Mann-Whitney U test in case of non-normal distribution. *P*-values of ≤0.05 will be considered statistically significant.

Categorical data will be displayed as numbers and percentages and analysed using a Chi-square test.

Investigational site, surgical procedure, age, and score on the eHealth literacy test will be taken into account as covariates in the adjusted analyses. Intended subgroup analyses will be conducted for the surgical procedure.

To estimate the primary outcome, the overall average compliance to the selected active ERAS elements, the elements will be scored as ‘completed’ or ‘not completed’ (dichotomous), as described by the ERAS protocol. For example, the urine catheter should be removed on day one after surgery. If this could not take place, the element was scored as ‘not completed’. For both the intervention and control groups, the proportion of completion of each individual active element will be calculated. The overall compliance is an average of the individual completion percentages. The protocol compliance is a continuous variable and will be reported as mean and standard deviation in case of normal distribution and as median and 95% confidence intervals in case of non-normal distribution.

The relation of the use of the application with the secondary outcomes mentioned in Table 5 will be examined with a linear regression.

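### Randomisation in a two-site trial is not stratified by site, which costs a little precision, and the age strata omit patients aged exactly 50

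*Protocol article*

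**What the plan says.** Group allocation and blinding describes individual allocation in equal numbers to the app or to usual care. The method and its strata are given as "using an internet randomization module with stratification for benign or malignant pathology and age (> 50 years and < 50 years". On blocking, the section adds: "Random block sizes of 2, 4, and 6 will be used". No other stratification factor is named.

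Study setting calls the trial a "multicentre RCT that will be conducted in the Amsterdam University Medical Centres (UMCs), locations AMC and VUMC". Study population sets only a lower age limit: "Patients must be 18 years or older and in possession of a smartphone".

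Three statements bear on whether site matters:
- Background, about ERAS in general: "Local ERAS protocols, based on the ERAS guideline, can vary depending to the performing medical centre".
- Content development, about the two trial sites: "Both locations practice almost all the elements from the 2012 ERAS society recommendations for colorectal surgery as part of their ‘care as usual". The same two exceptions are named for both locations.
- Data analyses: "Investigational site, surgical procedure, age, and score on the eHealth literacy test will be taken into account as covariates in the adjusted analyses". The same section gives the group comparison as a t-test or a Mann-Whitney test, and does not say whether the adjusted or the unadjusted result is primary.

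**The concern.** The control condition is whatever usual care each location delivers, and the authors consider site prognostic enough to adjust for. A factor of that kind, known before randomisation and with only two levels, is a natural stratum. Without it, one arm can by chance draw more of its patients from one location. If compliance differs between locations, the unadjusted difference between arms then carries part of that site difference, in a trial planned around 5 points.

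The age boundary is a separate and simpler matter. One stratum is above 50 and the other below 50. A patient aged exactly 50 meets the eligibility criteria and belongs to neither, so the rule as printed does not cover every eligible patient.

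**Working it through.** **The plan's own figure.** Inputs from Sample size calculation: difference 62 − 57 = 5 points, SD 9, two-sided alpha 0.05, power 90%.
- Normal approximation: n per group = 2 × [9 × (1.960 + 1.282) / 5]² = 68.1, so 69.
- With the t distribution, power is 0.8997 at 69 and 0.9038 at 70, so 70 per group.
- Loss of 10%: 140 / 0.9 = 155.6, so 156.

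The stated sample size reproduces, and nothing below changes it.

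**Site imbalance as the plan stands.** Two arms of 78 and sites split 50:50 (assumption; the documents give no split). If site is not a stratum, the difference between arms in site share has approximately

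SD = √(0.5 × 0.5 / 78 + 0.5 × 0.5 / 78) = √(0.5 / 78) = 0.080, or 8.0 percentage points.

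A simulation of 4,000 trials of 156 patients, with permuted blocks of 2, 4 and 6 within strata, agrees. Assumed shares: 60% malignant, 75% over 50.

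| Site split | Site a stratum? | SD of difference in site share | 95% of trials within | Difference above 10 points |
|---|---|---|---|---|
| 50:50 | no | 8.0 points | 15.5 points | 23% |
| 50:50 | yes | 1.8 points | 3.8 points | none of 4,000 |
| 70:30 | no | 7.3 points | 14.1 points | 17% |
| 70:30 | yes | 1.9 points | 3.8 points | none of 4,000 |

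**Effect on the unadjusted result.** Shift = difference in site share × difference in mean compliance between sites. The second term is not in the documents, so a range is assumed. At 50:50, a gap of g points between sites has variance (g / 2)², to be compared with the planning variance 9² = 81.

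| Assumed site gap in overall score | Share of planning variance | 95% limit of shift, no site stratum | 95% limit of shift, site a stratum |
|---|---|---|---|
| 2.5 points | 1.25² / 81 = 1.9% | 2.5 × 0.155 = 0.4 | 2.5 × 0.0375 = 0.1 |
| 5 points | 2.5² / 81 = 7.7% | 5 × 0.155 = 0.8 | 5 × 0.0375 = 0.2 |
| 10 points | 5² / 81 = 31% | 10 × 0.155 = 1.6 | 10 × 0.0375 = 0.4 |

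A 15-point gap would take 7.5² / 81 = 69% of the planning variance, which is hard to reconcile with an SD of 9, so it is left out. The 10-point row is already generous.

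**What the site covariate does.** In a site-adjusted linear model the shift is removed, and the remaining cost of imbalance is a variance inflation of 1 / (1 − d²), where d is the difference in site share at a 50:50 split. At the 95% limit, d = 0.155, this is 1.025, so 156 patients act like about 152. At one SD, d = 0.080, it is 1.006.

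**Age.** Eligible ages are 18 and over. The strata cover 18 to 49 and 51 upward, so age 50 is uncovered.

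**The case against.** The strongest reply is that site is already handled: it is a planned covariate, and with adjustment the loss is about 2.5% of precision in an unlucky trial and under 1% in a typical one. That stands. It does not close the point, because the comparison spelled out in Data analyses is unadjusted and the adjusted analysis is not named as primary.

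Second, the shift is ordinary random error. Allocation is individual and 1:1. If the SD of 9 is the total SD, variation between sites is already inside the planned standard error of 9 × √(2 / 70) = 1.52 points (95% half-width about 3.0). That also stands: the shifts above are part of that uncertainty, not an addition to it.

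Third, a reader might infer that usual care is known to differ between the two locations. The documents do not say so. The Background sentence is general and says only that local protocols can vary, while Content development describes the two sites jointly with identical exceptions. That text concerns which elements are practised, not how often they are completed, so a difference is possible but undocumented.

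Fourth, a reader might infer from Table 1 that site drives half the score, since five of the ten scored elements are marked Active/Passive. The label means only that both patient and staff contribute. Nothing shows that location determines completion.

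Finally, the age gap might be read as an opening for steering allocation, because the trial is unblinded and the coordinating researcher both approaches patients and initiates allocation. The text shows no such mechanism. An internet module needs some boundary in its settings, and a single year of age has a negligible effect on a 1:1 comparison.

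**Conclusion.** The point holds in a modest form. Leaving site out of the strata lets the arms differ in site share with an SD of about 8 percentage points, where about 2 is available almost free. On an assumed site gap of 2.5 to 10 points, the unadjusted result shifts by at most about 0.4 to 1.6 points in 95% of trials, against a 5-point target. The comparison is not biased, and the planned covariate recovers nearly all of the loss wherever the adjusted analysis is used. The size rests on three assumptions: an even site split (70:30 gives similar figures), the assumed stratum shares, and above all the site gap, on which the documents are silent.

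The age gap is certain and small: the strata as written are not exhaustive.

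**What to change.** - Add investigational site (AMC, VUMC) as a stratification factor in the internet module before enrolment starts.
- Make the age strata exhaustive, for example < 50 and ≥ 50 years, and check that the module uses the same boundary.
- Keep site as a covariate. It is also what lets the standard error reflect the added stratum; an unadjusted test would not.

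The cost is a module setting and one protocol line. The abstract says enrolment was still to come and data collection had not begun. The number of strata rises from 4 to 8, averaging 156 / 8 = 19.5 patients. Under the assumed shares the smallest would hold about 156 × 0.40 × 0.25 / 2 = 8. Blocks of 2, 4 and 6 can handle this, as the simulated SD of 1.8 points shows. If the strata can no longer be changed, naming the site-adjusted comparison as primary would secure most of the gain.

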### Data collection

Data from the intervention group will mostly be automatically collected and stored in the database. For instance, results from the self-reported questionnaires will be sent from the application to the database. Some data will be collected through the Electronic Health Record (EHR) by the coordinating researcher and entered in case report forms (CRFs). As for the control group, the data from the patient dairy, the self-registered questionnaires, and data from the activity tracker will be manually entered in the CRF. Trial findings will be stored in accordance with local data protection laws and handled in confidence. A data protection impact assessment has been part of the protocol.

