### Outcomes

The primary outcome is the overall average compliance to the selected active ERAS elements (Table 2). Since the application is patient-centred and focusses on empowering patients to get in control of their own health, the PROMs, such as health related quality of life and patient satisfaction, are considered important secondary outcome parameters. Other secondary outcomes include postoperative outcome parameters (e.g. complications), gastro-intestinal recovery (e.g. time to passage of stool), activity and pain measurements. Table 5 describes all study outcomes and how and when these will be measured.

**Table 5 Tab5:** Time points and measurements

Enrolment		T0	T1	T2	T3	T4	T5	T6	T7	Registered in/with:
	Eligibility screen	x								
	Informed consent	x								
	Allocation	x								
Interventions		T0	T1	T2	T3	T4	T5	T6	T7	
Intervention group	Download mobile application	x								
	Wear activity tracker		O	O	O	O	O	O		
Control group	Wear activity tracker		O	O	O	O	O	O		
Data measurements		T0	T1	T2	T3	T4	T5	T6	T7	
Baseline characteristics	General characteristics	x								Sex, age, ASA, BMI, smoking, alcohol intake
	Disease related characteristics	x								Disease, operation
	eHealth literacy assessment	x								eHEALS
Protocol compliance *(as reported by patients)*	1. Cessation of smoking and excessive intake of alcohol	x								Y/N questions in app or with paper form
	2. Preoperative nutritional screening and, as needed, assessment and nutritional support	x								Y/N questions in app or with paper form
	3. Preoperative carbohydrate treatment			x						Y/N questions in app or with paper form
	4. Preoperative prophylaxis against thrombosis			x						Y/N questions in app or with paper form
	5. Early mobilization (day of surgery)				O	O				Y/N questions in app or with paper form
	6. Early intake of oral fluids and solids (offered the day of surgery)				O	O				Y/N questions in app or with paper form
	7. Early removal of urinary catheters and intravenous fluids (morning after surgery)					O				Y/N questions in app or with paper form
	8. Use of laxatives					O				Y/N questions in app or with paper form
	9. Intake of protein and energy-rich nutritional supplements					O				Y/N questions in app or with paper form
	10. Prepare for early discharge					O				Y/N questions in app or with paper form
Postoperative data ≤30 days *(retrospective collection)*	Length of hospital stay								x	EHR
	Overall morbidity ≤30 days								x	EHR

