	Complications								x	Clavien-Dindo minor: I-II major: III-V
	Reoperations								x	EHR
	Readmission ≤30 days								x	EHR
	In-hospital mortality								x	EHR
Gastrointestinal	Tolerance of solid food				O					Days
	Absence of nausea				O					Days
	Passage of first flatus				O					Days
	Passage of first stool				O					Days
	Weight - preoperative			x						Weight at admission, KG
	Weight - at discharge				x					Weight at discharge, KG
Activity	Mean preoperative physical activity (steps/day)		O							Activity tracker, steps per day
	Postoperative physical activity (steps/day)				O	O	O			Steps per day
Pain	Perceived pain daily postoperative - discharge				O					NRS 1–10*
	Compliance with intake of (pain) medication				O					Y/N questions in app or with paper form
Self-registered questionnaires		T0	T1	T2	T3	T4	T5	T6	T7	
PROMS	General quality of life (WHOQol)	x				x	x		x	WHOQoL - BREF
	Multidimensional fatigue assessment	x						x	x	Multidimensional fatigue inventory
	Physical Activity (IPAQ)	x				x		x	x	IPAQ-short
	Disability	x							x	WHODAS2
	Patient satisfaction questionnaire								x	Self-developed patient satisfaction questionnaire

T0: Moment of randomization; T1: 1–7 days before stay in hospital; T2 hospital admission; T3: day of surgery; T4: 1–7 days after surgery; T5: 8–14 days after surgery; T6: 15 days – 21 days after surgery; T7: 22–42 days after surgery

x: the event/action is performed or assessed once in the indicated time slot. O: the event/action is performed or assessed continuously in the indicated time slot. *Numeric rating scale

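### The protocol does not place the T0 self-report measures, including the eHEALS covariate, before open-label allocation

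*Protocol article*

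**What the plan says.** In the Outcomes section, the T0 column of Table 5 holds the eligibility screen, consent, allocation, the eHEALS and the first WHOQoL-BREF, fatigue inventory, IPAQ-short and WHODAS2. For the intervention arm it also holds the row "Download mobile application". The footnote defines the column as "T0: Moment of randomization" and explains the x symbol: "the event/action is performed or assessed once in the indicated time slot". It gives no order within the slot.

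The Recruitment section sets the sequence: "After obtaining written consent, participants will be randomized". It mentions no baseline assessment between these two steps. Under Group allocation and blinding: "Participants, professionals of the healthcare team, and outcome assessors will not be blinded to the treatment allocation".

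On the route, the Data collection section says of the intervention arm that "results from the self-reported questionnaires will be sent from the application to the database", whereas the control arm's questionnaires are keyed into the CRF by hand. The APPtimize study group section gives the app to the intervention arm only, and its dashboard tracks questionnaire completion over the whole study.

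On use, the Data analyses section states: "Investigational site, surgical procedure, age, and score on the eHealth literacy test will be taken into account as covariates in the adjusted analyses". It also plans a comparison of baseline characteristics between arms.

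**The concern.** A baseline measure can serve for adjustment, or for judging whether the arms are comparable, only if allocation cannot have influenced it. The eHEALS asks patients to rate their own eHealth skills. In an unblinded trial, a patient who has just been given a health app, or has just learned that they will not get one, may answer differently. Self-rated wellbeing, fatigue and activity could move in the same way. If the arms also answer by different routes, a mode effect is added to any allocation effect.

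Three things are at stake:
- **Adjusted analyses.** A covariate that allocation has shifted removes part of the treatment effect or adds to it.
- **Baseline comparison.** A difference caused by allocation or mode would look like chance imbalance.
- **Completeness.** The app displays questionnaire completion and the controls have no app, so the share of patients with a baseline could differ by arm.

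Analysis cannot repair a contaminated baseline afterwards.

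**Working it through.** **Is there a stated figure to reproduce?** None bears on this point. The sample size is sound on its own terms: a difference of 5 (57% to 62%), SD 9, two-sided 0.05 and 90% power give 69.06 per arm by the t-test, rounded up to 70, and 140 / 0.9 = 155.6, rounded up to 156. Moving the baseline does not change it.

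**Order, step by step**
1. Table 5 ties T0 to randomisation, not to a visit before it.
2. The Recruitment section leaves no questionnaire step between consent and randomisation.
3. The Prognostic factors section calls its baseline preoperative, which places it before surgery but not before allocation.
4. Intervention-arm questionnaires come through the app, with no exception stated for T0.
5. Only patients allocated to the intervention have the app. Any questionnaire completed in it therefore follows allocation and download.
6. Table 5 also schedules compliance elements 1 and 2 at T0, answered in the app or on a paper form. So T0 does include data captured after download, by a different mode in each arm.

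Steps 1 to 3 show that nothing puts the T0 measures first. Steps 4 to 6 imply that the intervention-arm questionnaires come second. For controls, and for the eHEALS in either arm, the order is simply open.

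**What a shift would do (illustration; inputs assumed, not in the documents)**

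Let b be the shift in the T0 score in one arm, in SD units, and rho the within-arm correlation of that score with the outcome. Take the shift as additive and the SD as equal at both times.
- Follow-up score without baseline: bias 0.
- Change score: bias = -b.
- Baseline-adjusted: bias of about -rho × b.

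| b | change score | adjusted, rho = 0.3 | adjusted, rho = 0.5 | adjusted, rho = 0.7 |
|---|---|---|---|---|
| 0.1 | -0.1 | -0.03 | -0.05 | -0.07 |
| 0.2 | -0.2 | -0.06 | -0.10 | -0.14 |
| 0.3 | -0.3 | -0.09 | -0.15 | -0.21 |

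**The same formula for the eHEALS in an adjusted analysis of compliance.** Multiply by the planning SD of 9 percentage points, with rho now the correlation of eHEALS with compliance.
- rho = 0: no bias.
- rho = 0.3: 0.3 × 0.1 × 9 = 0.27 to 0.3 × 0.3 × 9 = 0.81 points.
- rho = 0.7: 0.7 × 0.1 × 9 = 0.63 to 0.7 × 0.3 × 9 = 1.89 points.

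The planned difference is 5 points. If allocation raises the score in the app arm and a higher score goes with better compliance, the adjusted effect is understated. The documents give neither b nor rho, so these figures show only how the bias scales.

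**The case against.** The strongest reply is that an unstated order is not a wrong order. The T0 column also contains screening and consent, which plainly precede randomisation, so a place in that column does not prove that a form came after allocation. The Data collection section says only that intervention-arm data are mostly captured automatically, and it offers the questionnaires as an example. Table 5 lists the eHEALS with sex, age and BMI rather than in the questionnaire block, and the Prognostic factors section says that it will be assessed in a standardised way. The article is condensed, and the sequence of forms at enrolment may be fixed in the full protocol.

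Much of this stands, and it limits what can be claimed. A reader might infer that all baseline questionnaires are completed after allocation, with controls answering on paper and knowing that they did not get the app. The documents do not say so: no order is given for controls, and a paper form is named for compliance and medication items but not for these questionnaires. A reader might also infer that the questionnaire effects carry a bias of known size. The Data analyses section names no change score and no baseline questionnaire score as covariate, and a comparison of follow-up scores alone would escape this bias.

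The reply does not remove the point. The article is not silent on order: it fixes T0 at randomisation, runs from consent directly to randomisation, and routes one arm's questionnaires through a tool that only that arm receives. Standardised assessment of the eHEALS answers the question of mode at most, not of timing.

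**Conclusion.** The point holds in a limited form. As written, the protocol does not protect any T0 self-report measure from knowledge of allocation. For the intervention arm, it implies that the baseline questionnaires follow allocation and app download, by a different route from the controls. That implication assumes that the general statement on in-app questionnaires covers T0.

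The direct exposure is the eHEALS as a named covariate, together with the comparison of baseline characteristics. Bias in the questionnaire outcomes is conditional on an analysis that the article does not specify, although collecting the same instruments at T0 and later makes such a use foreseeable. The size cannot be derived from the documents. The unadjusted comparison of compliance contains neither the eHEALS nor a baseline questionnaire score, so this does not undermine the main primary comparison. It is an inexpensive improvement worth making before enrolment; the abstract states that data collection had not begun.

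**What to change.** In Table 5, split T0 into two columns: one after written consent and before randomisation, and one for allocation and app download. Place the eHEALS, WHOQoL-BREF, fatigue inventory, IPAQ-short and WHODAS2 in the first, completed by every participant in the same mode (one paper form or one web form). In the Recruitment section, add that the randomisation module is opened only once these forms have been received.

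The instruments and the sample size stay as they are. The cost is a short delay before randomisation. It matters most for patients with early surgery dates, since the protocol already allows at least 72 hours for the decision and foresees some patients with fewer than 7 days before surgery. Some patients may also be lost before randomisation because they do not return the forms. If gating on receipt is judged too strict, one sentence that fixes the order and a common mode would secure most of the benefit.
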